**Outcome assessment**

**Primary outcome**

There is one primary outcome measure: 1) Average pain in the previous week.

1) Pain intensity will be assessed at baseline and after treatment in 8 weeks. They will also be evaluated at 60 weeks, which is a secondary time point for the primary outcome. Pain intensity will be assessed using the visual analogue scale (VAS)^5^. Formed by a 100 mm horizontal line, anchored by the words “no pain/discomfort” and “worst imaginable pain/discomfort”^5^. To measure pain, the participant will be asked to indicate the level of pain they are currently feeling and the average pain they felt in the last week, marking the scale with a line. A ruler will be used to measure the obtained value^5^.

**Secondary outcomes**

There are seven secondary outcome measures: 1) Perceived Global Effect, 2) Muscle Strength, 3) Pain Catastrophizing, 4) Kinesiophobia, 5) Central Sensitization, 6) Muscle Recruitment, and 7) Hip Functionality.

1) The global perceived effect scale (GPE) will be used after treatment at 8 and 60 weeks^21^. This is a 7-point scale (1=completely recovered, 7=worse than ever) to assess recovery. GPE assesses the participant's perception regarding the modification of their clinical condition after the intervention, and is evaluated by a simple and easy-to-understand question with alternative answer options that will be dichotomized into "improved" ("completely recovered" and "much better ") versus “not improved” (“slightly improved”, “not changed”, “slightly worse”, “very much worse”, “worse than ever”^21^.

2) Isometric strength of the hip abductor and extensor muscles will be assessed at baseline and after treatment, 8 weeks during post-intervention reassessment. A manual dynamometer model Lafayette (Lafayette Instruments) will be used, which has proven to be a valid method for evaluating isolated muscle contraction strength^22^. To assess the hip abductor musculature, participants will be placed in the supine position on a stretcher, stabilized by velcro bands around the pelvis and above the lateral ankle malleolus to avoid compensatory movements and the influence of the assessor resistance^22^. The dynamometer will be positioned above the lateral ankle malleolus and fixed to the stretcher by an inelastic strap, it will be positioned without rotation, with 10º of hip abduction to minimize the potential for compression of the tendons against the greater trochanter^14^. The untested lower limb will be positioned with 45º of hip and knee flexion, with the foot positioned on the stretcher and the upper limbs supported by the side of the body (figure 2)^14^. For evaluation of the hip extensors, participants will be positioned in the prone position with knee flexion on the lower limb to be evaluated. The dynamometer will be positioned on the posterior region of the thigh, above the popliteal fossa and will be stabilized by an inelastic velcro strap^23^. Another Velcro strap will be placed around the pelvis (figure 3)^23^. The measurement of limb length will be performed with a measuring tape to calculate torque, from the greater trochanter to the center of the dynamometer, and will be recorded in meters^23,24^. The maximum voluntary contraction tests will be performed 3 times with 5 seconds of duration for each contraction, with 30 seconds of rest between each attempt^23^. Participants will be verbally encouraged to perform as much strength as possible during the test. The strength values ​​will be normalized by the weight of each participant^23^.

Figure 2. Assessment of isometric strength of hip abductor muscles

[figure not shown]

Figure 3. Evaluation of isometric strength of hip extensors muscles

[figure not shown]

3) Pain catastrophizing will be measured with the Pain Catastrophizing Scale (PCS) at baseline and after treatment, at 8 and 60 weeks during post-intervention reassessment. The PCS is a validated^25^, self-administered, 13-item questionnaire that assesses catastrophic thoughts, feelings and behavior when in pain^25^. This questionnaire assesses three main domains: helplessness, magnification and rumination in relation to pain. Results are calculated as the sum of all survey items and total scores range from 0 to 52, with higher scores indicating higher levels of pain catastrophizing^25^.

4) Kinesiophobia will be assessed with the Tampa scale of kinesiophobia, which is a validated, self-administered questionnaire with 17 questions and translated into Portuguese. Kinesiophobia will be assessed at baseline and after treatment, at 8 and 60 weeks during post-intervention reassessment. The final score can be at least 17 and at most 68 points, with higher scores indicating higher degrees of kinesiophobia^26^.

5) Central sensitization will be measured with the central sensitization inventory, which is a self-administered health symptoms questionnaire designed as an easy-to-administer tracker for patients at high risk of central sensitization or to assess symptoms related to central sensitization^27^. Central sensitization will be measured at baseline and after treatment at 8 and 60 weeks during post-intervention reassessment. It has also been recommended as a component of an algorithm to help classify chronic pain patients with central sensitization and to help differentiate them from patients with primary neuropathic and nociceptive pain^27^.

6) Muscle recruitment during treadmill walking (MOVEMENT^®^) will be assessed at baseline and after treatment at 8 weeks follow-up. Surface electromyography will be used in three different walking conditions: preferential speed, top speed but no running and 3.0km/h. Each speed will be recorded for one minute. The familiarization with the treadmill will be carried out for 5 minutes at the self-selected speed, the interval between each test of each speed will be 1 minute and the participants will take the test barefoot^13^. The electromyographic signals will be captured using an 8-channel biological signal acquisition model module (New Miotool Wireless, Porto Alegre, Brazil) with 2000 gain, 16-bit A/D converter, 1010 Ohm / 2 pF input impedance , common mode rejection ratio 126 dB, bandpass filter 20–500 Hz and sampling rate 2 kHz. In addition, the software allows real-time filming via the webcam. All wires will be joined and secured to avoid motion artifact. The muscles of each participant will be located, according to the SENIAM group, and the electrodes will be placed unilaterally on the affected side (or more painful if bilateral) and longitudinally oriented with the muscle fibers of the muscle to be evaluated^10,13^. Trichotomy will be performed in the area of ​​electrode placement and skin abrasion with gauze to reduce impedance, in addition to the use of alcohol to clean the skin^13,14,15^. Active bipolar electrodes will be used, which will be placed in a bipolar configuration, with a capture area of ​​1cm in diameter and a distance of 2cm between them^13,14^. A reference electrode will be placed over the ulnar styloid process. The muscles evaluated are:

- Gluteus medius (GMED): electrodes will be placed 50% along a line from the iliac crest to the most lateral point of the greater trochanter.
- Gluteus maximus (GMAX): The electrodes will be placed 50% along a line between the sacral vertebrae and the most lateral point of the greater trochanter. This position corresponds to the greatest prominence of the middle of the buttocks, well above the visible bulge of the greater trochanter.
- Tensor fascia latae (TFL): The electrodes will be placed proximally 1/6 of the way along a line from the anterosuperior iliac spine (ASIS) to the lateral femoral condyle.

7) Hip functionality will be measured using the Victorian Institute of Sport Assessment questionnaire for gluteal tendinopathy (VISA-G) and will be assessed at baseline and after treatment, 8 and 60 weeks during post-intervention reassessment. This is a self-administered questionnaire, translated, culturally adapted and validated for the Portuguese Brasileiro^33^. Visa-G is specific to assess the severity of deficiency in people with gluteal tendinopathy. It is an 8-item questionnaire that assesses pain and function. Scores range from 0 to 100 and higher values ​​indicate less pain and better functionality^33^.

7) Hip-related disability will be measured with the Hip Outcome Score (HOS), which is a self-administered questionnaire to assess young, physically active or both patients with hip disorders. It consists of 28 items divided into two subscales: activities of daily living and sports activities. The total score for each subscale ranges from 0 to 100, where higher scores denote better hip function. The scores for each subscale were calculated separately^34^.

7) Disability will also be assessed using the International Hip Outcome Tool (iHOT) which is a 12-question self-administered questionnaire. The questions are evaluated using a visual analogue scale, so each question has a 10 cm line and the participants must add a vertical line crossing the horizontal line, and the farther to the left, the worse the symptoms. The result of each question can vary between 0 and 100 and to determine the result, all the questions must be added and divided by the number of answered questions^35^.

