**Sample size and power analysis**

Sample calculation was performed using the G * Power software, based on the measure of the level of pain, as it is the primary outcome of the research. A power of 0.80, error probability α 0.05, effect size of 0.5 and dropout rate of 15% were used, for this we will recruit 60 participants (30 in each group)^9^.

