**Statistical analysis**

The study will be run as a superiority trial. The statistical analysis will follow the intention-to-treat concept. Statistical analysis will be performed using the software IBM SPSS Statistics for Windows, version 20.0 (IBM Corp., Armonk, N.Y., USA) and statistician will be blind. Data will be evaluated using exploratory statistical techniques. Firstly, the normality and homogeneity of the data will be verified and then the appropriate statistical analyses will be adopted for the variables. The between-group differences and their respective confidence intervals at 95% will be calculated by constructing mixed linear models interaction of group data versus time. The linear mixed-effect model will be applied to the primary and secondary outcomes. “Time” and “group” will be considered fixed effects, whereas the participants will be considered random effect. The dependent variable baseline values will be included as a covariate for the correction of possible baseline between-group differences.

A causal mediation analysis will be conducted using the “mediate” package in R (The R Foundation for Statistical Computing). A model-based inference approach will be used to estimate the average causal mediation effect (ACME), average direct effect (ADE) and the average total effect^29^.

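### Cutting the seven-level global perceived effect score to improved versus not improved discards order information and costs roughly 4 to 13 points of power under stated assumptions: an avoidable efficiency loss, not an error

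*Protocol*

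**What the plan says.** Secondary outcomes, item 1, sets the timing: "The global perceived effect scale (GPE) will be used after treatment at 8 and 60 weeks". It describes the instrument: "This is a 7-point scale (1=completely recovered, 7=worse than ever) to assess recovery". It then reduces the answers: "alternative answer options that will be dichotomized into 'improved" for the best two levels, with the remaining five levels forming the other class. A reference to an earlier trial supports the definition. No ordinal form of GPE is planned anywhere in the protocol.

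The only effect size is under Sample size and power analysis: "A power of 0.80, error probability α 0.05, effect size of 0.5 and dropout rate of 15% were used". That section ties the calculation to pain: "based on the measure of the level of pain, as it is the primary outcome of the research". The resulting size is "we will recruit 60 participants (30 in each group"). The Introduction states the hypothesis that both groups will improve on all outcomes, with motor control superior.

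**The concern.** Seven ordered answers become two. Complete recovery counts the same as a large improvement, and a slight improvement counts the same as the worst possible answer. Both arms receive active exercise and both are expected to improve, so the arms may differ mainly in degree. A difference on one side of the threshold, or worsening in one arm, cannot show in the binary variable.

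The protocol fixes this choice itself, so it is not a detail left to a later analysis plan. It is also separate from the choice of model, because a correct binary model would carry the same loss. At stake is the chance of detecting a real difference in patient-rated recovery with about 51 women.

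**Working it through.** **1. The plan's own figure.** There is none for GPE. The stated 60 belongs to pain. A two-sample t test with d = 0.5, two-sided 0.05 and power 0.80 needs 64 per arm, or 64/0.85 = 75.3, so 76 after dropout. One-sided it needs 51 per arm, or 51/0.85 = 60 per arm. The total of 60 is therefore not reproduced. With 30 per arm, two-sided power for d = 0.5 is about 0.48; with about 26 per arm it is about 0.42. That last figure is a benchmark for a continuous, normally distributed outcome.

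**2. Inputs.**
- Evaluable women: 60 × 0.85 = 51, or 25.5 per arm (protocol).
- Shift: 0.5 SD on a latent GPE scale. This is an assumption carried over from pain.
- Two-sided alpha 0.05. The protocol does not state sidedness.
- Comparator improved rate: 30% to 70%. This is an assumption, as is the spread over the seven levels.
- One time point, arms compared directly.

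**3. Binary form, 50% of comparators improved, latent normal shift.**
- The other arm's rate is Φ(0 + 0.5) = 0.691, so the difference is 0.191 and the mean rate 0.596.
- SE under no difference = √(2 × 0.596 × 0.404/25.5) = 0.137.
- SE under the alternative = √((0.500 × 0.500 + 0.691 × 0.309)/25.5) = 0.135.
- Power = Φ((0.191 − 1.96 × 0.137)/0.135) ≈ 0.28.

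Simulation of the tie-corrected Mann-Whitney test on all seven levels gives 0.37 in the same setting.

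**4. Same check under proportional odds (Whitehead formula).**
- A shift of d = 0.5 corresponds to a log odds ratio of 0.5 × π/√3 = 0.907, an odds ratio of 2.48.
- Assumed comparator levels: 12, 38, 30, 12, 5, 2 and 1%. The other arm's improved rate becomes 0.712.
- Averaging the two arms by level, the sum of cubed proportions is 0.0965.
- V = (51/12) × (1 − 0.0965) = 3.84.
- Ordinal power = Φ(0.907 × √3.84 − 1.96) = Φ(−0.183) = 0.427.
- The binary formula with 0.500 versus 0.712 gives 0.338. The loss is 8.9 points.

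**5. Range.** Power at 51 women, binary / ordinal. Coarse means that answers cluster in two or three levels. The two columns assume the same improved rates but were set up separately at the other levels.

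| Comparator improved | Simulated, latent normal, 26 v 25 | Proportional-odds formula, 25.5 per arm |
|---|---|---|
| 30% | 0.280 / 0.381 | 0.342 / 0.444 |
| 40% | 0.292 / 0.379 | 0.353 / 0.438 |
| 50% | 0.278 / 0.370 | 0.338 / 0.427 |
| 60% | 0.279 / 0.367 | 0.303 / 0.418 |
| 70% | 0.248 / 0.365 | 0.253 / 0.417 |
| 40%, coarse | not run | 0.353 / 0.398 |
| 50%, coarse | 0.284 / 0.349 | 0.338 / 0.396 |
| 60%, coarse | 0.277 / 0.333 | not run |

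A second simulation with 25 or 26 per arm gave losses of 4.4 to 10.7 points over 30% to 70%. Taken together the loss is roughly 4 to 13 points. The one cell above that is the 70% row under proportional odds, at 16 points. With no shift, both simulated tests reject in 4.6% to 5.3% of trials, so the gain is not bought with type I error.

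**6. Outside the central range.** At 10% improved the loss is about 17 points (latent normal) or 24 points (proportional odds). If the binary comparison uses Fisher's exact test, the loss over 30% to 70% is about 14 to 21 points.

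**7. In women rather than points.** Take 0.28 versus 0.37. The standardised effects are 1.96 − 0.583 = 1.377 and 1.96 − 0.332 = 1.628. The squared ratio is 0.72, so the cut discards about 28% of the information, comparable to losing about 14 of the 51 women for this outcome.

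**The case against.** The strongest reply is that this is a preference. The responder definition is set in advance, assigns every level to a side and cites a source. If both arms are expected to improve, a threshold that excludes slight improvement asks a sensible question: which arm gives substantial recovery? This stands. A reader might infer that the cut is a mistake or contradicts another section; the protocol does not support that.

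A reader might also take the loss as one at the protocol's own effect size. It is not. The 0.5 is for pain, its metric is unstated, and no GPE distribution is given. The range is conditional on all of this and on the test used.

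Third, GPE stays underpowered either way. This also stands: the ordinal figures are only about 0.33 to 0.44, and the sample size is the larger problem.

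Fourth, the Statistical analysis section says "The linear mixed-effect model will be applied to the primary and secondary outcomes", and the check models a single-time comparison instead. That is fair as to exact figures. How a linear mixed model suits a binary outcome with no baseline value is a separate question, and no choice of model restores order that the cut has removed.

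Finally, worsening can still be tabulated from the recorded levels, and pain and hip function are measured on full scales. True, but tabulation does not recover the information in the comparison between arms.

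**Conclusion.** The point holds as an avoidable loss of efficiency on one secondary outcome. Under a 0.5 SD latent shift, 51 evaluable women, two-sided 0.05 and 30% to 70% of comparators improved, the cut lowers power by roughly 4 to 13 points, and by more at extreme improved rates or with Fisher's exact test. The size depends on assumptions that the protocol does not supply. The direction did not change in any scenario tried.

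It does not follow that the responder outcome is invalid or should be dropped, nor that an ordinal analysis would give GPE adequate power.

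**What to change.** In Secondary outcomes, item 1, state that the arms are compared on the full seven-level GPE score at 8 and 60 weeks, by the Wilcoxon-Mann-Whitney test or by a proportional-odds model reporting a common odds ratio with 95% CI. Keep the improved proportion per arm, with its risk difference and 95% CI, reported beside it.

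The cost is a wording change and one more line of analysis, since all seven levels are already collected. The downside is small. A common odds ratio is less familiar to clinicians, and the model assumes roughly proportional odds, which is hard to check with about 25 women per arm and sparse levels. The rank test and the retained responder rate limit both problems.

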**Analysis of electromyographic data**

The electromyographic analysis will be performed using Matlab® software. The fourth-order Butterworth high-pass filter with a cut-off frequency of 20 Hz, the fourth-order Butterworth low-pass filter with a cut-off frequency of 500 Hz, full-wave signal rectification and a low-pass filter of 6 Hz will form the linear envelope. The values ​​of the linear envelope of the muscles will be normalized by the highest value obtained in the maximum voluntary isometric contraction (MVIC) in the assessment and reassessment of their respective muscles.

**Interventions**

**Motor Control Group (MCG)**

The motor control program will be carried out over 8 weeks, with two weekly appointments, face-to-face and individualized. There will be a total of 16 sessions, each lasting from 50 to 60 minutes. The protocol will consist of isotonic and isometric strengthening exercises, focusing on the abductor and hip extensor muscles with coordination through verbal commands to improve dynamic motor control of the lower limbs. Exercise progression will occur through elastic bands, from the easiest to the most difficult, and with the addition of more difficult exercises^23^. In the first week there will be no use of loads, but from the second week on, the MCG will be tested with three different colors of elastic bands, from the easiest to the most difficult, and they will be instructed to perform 3-5 repetitions with each band^23^. They will decide which elastic band they feel would be able to perform 3 sets with 8-12 repetitions, maintaining movement quality^23^. The participants will choose the elastic color for each exercise and the elastic will be positioned above the knee joint. The load progression test will be performed weekly and the load progression will be increased according to the modified Borg scale (0-10), when 3 (moderate) or lower scores (easy) are reached, the load progression will be performed for the elastic subsequent^23^. Rest between exercises will be one minute^28^.

As for the evolution of the exercises, if the participants are unable to progress due to enough pain to give up the exercise, or difficulty in performing at least 8 repetitions with quality, they will remain with the parameters they were able to perform.

**General exercises group (GEG)**

GEG will carry out training over 8 weeks, with two weekly sessions, face-to-face and individualized. There will be a total of 16 sessions, each lasting from 50 to 60 minutes. The protocol will consist of a 5-minutes walking warm-up, stretching and strengthening the muscle groups of the trunk, hip and lower limbs. Exercise progression will occur through elastic bands, from the easiest to the most difficult, and with the addition of more difficult exercises^23^. In the first week there will be no use of loads, but from the second week on, the GEG will be tested with three different colors of elastic resistance range, from the easiest to the most difficult and oriented to perform 3-5 repetitions with each range^23^. They will decide which elastic band they consider would be capable of performing 3 sets with 8-12 repetitions, maintaining movement quality^23^. Participants will choose the rubber band color for each exercise, and the band will be positioned above the knee joint. The load progression test will be performed weekly and the load progression will be increased according to the modified Borg scale (0-10), when 3 (moderate) or lower scores (easy) are reached, the load progression will be performed for subsequent elastics^23^. Rest between exercises will be one minute^28^. As for the evolution of the exercises, if the participants are unable to progress due to enough pain to give up the exercise, or difficulty in performing at least 8 repetitions with quality, they will remain with the parameters they were able to perform.

**Statistical analysis**

The study will be run as a superiority trial. The statistical analysis will follow the intention-to-treat concept. Statistical analysis will be performed using the software IBM SPSS Statistics for Windows, version 20.0 (IBM Corp., Armonk, N.Y., USA) and statistician will be blind. Data will be evaluated using exploratory statistical techniques. Firstly, the normality and homogeneity of the data will be verified and then the appropriate statistical analyses will be adopted for the variables. The between-group differences and their respective confidence intervals at 95% will be calculated by constructing mixed linear models interaction of group data versus time. The linear mixed-effect model will be applied to the primary and secondary outcomes. “Time” and “group” will be considered fixed effects, whereas the participants will be considered random effect. The dependent variable baseline values will be included as a covariate for the correction of possible baseline between-group differences.

A causal mediation analysis will be conducted using the “mediate” package in R (The R Foundation for Statistical Computing). A model-based inference approach will be used to estimate the average causal mediation effect (ACME), average direct effect (ADE) and the average total effect^29^.

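### The baseline-adjusted linear mixed model is assigned to all secondary outcomes, but dichotomised GPE has no baseline, so the stated analysis cannot be fitted to it and is of the wrong type

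*Protocol*

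**What the plan says.** The Secondary outcomes section of the protocol opens "There are seven secondary outcome measures: 1) Perceived Global Effect". On timing it says "The global perceived effect scale (GPE) will be used after treatment at 8 and 60 weeks", and no baseline assessment is given. The instrument is a seven-point scale, "with alternative answer options that will be dichotomized into" improved (the two best categories) and not improved (the other five).

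The Statistical analysis section describes one model. Between-group differences and their 95% confidence intervals "will be calculated by constructing mixed linear models interaction of group data versus time". Time and group are fixed effects, "whereas the participants will be considered random effect". The scope is "The linear mixed-effect model will be applied to the primary and secondary outcomes", with no exception. On adjustment it says "The dependent variable baseline values will be included as a covariate for the correction of possible baseline between-group differences". No logistic, GEE, generalised mixed or risk-ratio method is named anywhere in the protocol.

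**The concern.** The two sections cannot both be followed for GPE. One makes it a yes/no variable that exists only after treatment. The other requires a linear model that contains its baseline value.

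Because the stated analysis fails, someone has to choose a replacement later: the seven-point score or the dichotomy, a linear or a logistic model, which covariate if any, and which effect measure. Those choices could change what is concluded about patient-reported recovery, in a trial of 60 people in which participants know their allocation. This is more than detail left for a statistical analysis plan, because the protocol positively assigns a model and that model does not suit the outcome.

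**Working it through.** The protocol gives no figure for GPE, so there is none to reproduce. The check compares the two sections and then sizes the consequence.

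**1. Side by side**

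| Feature | Model in Statistical analysis | GPE in Secondary outcomes |
|---|---|---|
| Response type | Linear mixed model (Gaussian) | Two categories |
| Baseline of the outcome | Required covariate | Not measured |
| Visits available | Baseline plus follow-up | 8 and 60 weeks |

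The missing baseline is not an oversight in scheduling. The protocol says "GPE assesses the participant's perception regarding the modification of their clinical condition after the intervention", so a pre-treatment value cannot exist.

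**2. The model as written**

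Take simulated data for 60 participants with binary GPE at 8 and 60 weeks (response probabilities assumed): 60 × 2 = 120 records. With the GPE baseline in the model, 0 of 120 records are complete and the fit fails. A logistic GEE with group, time and group × time and no GPE baseline uses all 120.

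**3. The model without the covariate**

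On the same data the linear mixed model then runs.
- At 8 weeks its group contrast is 0.300. The GEE gives logits −0.268 and −0.268 + 1.280 = 1.012, i.e. proportions 0.433 and 0.733, difference 0.300.
- At 60 weeks the linear contrast is 0.300 − 0.167 = 0.133. The GEE logits are −1.190 and −0.547, i.e. 0.233 and 0.367, difference 0.133.

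So the linear contrast is the risk difference. What remains wrong is the variance assumption.

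**4. Unequal variances between arms at one visit**

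Inputs: 30 per arm and 15% dropout (Sample size and power analysis), 30 × 0.85 = 25.5, taken as 26 per arm. Assumed rates: 24/26 = 0.923 in one arm and 0.50 in the other.
- Variances p(1 − p): 0.071 and 0.25.
- Separate: SE = √(0.071/26 + 0.25/26) = 0.111.
- Pooled: mean variance (0.071 + 0.25)/2 = 0.1605; SE = √(2 × 0.1605/26) = 0.111.
- Difference 0.423; 95% CI 0.423 ± 1.96 × 0.111, about 0.21 to 0.64.

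With equal arms the two standard errors agree.

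**5. Unequal variances between visits**

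The model with a participant random effect has one total variance for both visits. With complete data this is roughly the mean of the two visit variances. Assume the same rate in both arms at each visit and 26 per arm, so SE = √(2v/26).

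For 50% at 8 weeks and 90% at 60 weeks:
- v = 0.25 and 0.09; common v = (0.25 + 0.09)/2 = 0.17.
- Model SE at both visits: √(0.34/26) = 0.114.
- Binomial SE: √(0.50/26) = 0.139 at 8 weeks; √(0.18/26) = 0.083 at 60 weeks.
- Ratios: √(0.17/0.25) = 0.82, about 18% too small; √(0.17/0.09) = 1.37, about 37% too large.

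The rates are assumptions, so here is a range (the ratios do not depend on the number per arm):

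| 8 weeks → 60 weeks | Visit variances | Common v | SE error at 8 weeks | SE error at 60 weeks |
|---|---|---|---|---|
| 50% → 50% | 0.25, 0.25 | 0.25 | none | none |
| 30% → 70% | 0.21, 0.21 | 0.21 | none | none |
| 50% → 70% | 0.25, 0.21 | 0.23 | 4% too small | 5% too large |
| 50% → 80% | 0.25, 0.16 | 0.205 | 9% too small | 13% too large |
| 50% → 90% | 0.25, 0.09 | 0.17 | 18% too small | 37% too large |

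**The case against.** Three arguments carry weight.

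- **The text may leave room.** The Statistical analysis section says in general terms that suitable analyses will be chosen once normality and homogeneity have been checked. That shows an intention to fit method to variable. But the sentence comes before the model is named, is tied to those distributional checks, and mentions neither GPE nor any binary method. The later, specific sentence then covers all secondary outcomes. A separate statistical analysis plan could name a GPE model, but only by departing from that sentence.
- **Any analyst would drop the covariate.** This is likely, and the failure would be obvious at once rather than silently wrong. So the statement that the analysis cannot be fitted applies to the model as written, not to every linear model. It still leaves the replacement to be chosen after the fact.
- **The linear model then does little harm.** This stands for the comparison of equal arms at a single visit (step 4). It does not stand across visits when response rates differ in a way that changes the variance (step 5).

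A reader might go further and infer that the linear model gives a mere coefficient instead of a comparison of responders. It does not: the contrast is the difference in proportions improved (step 3). A reader might also point to limits above 100%. For 24/26, the ordinary single-arm limit is 0.923 + 1.96 × 0.052 = 1.026. But the protocol plans intervals for between-group differences, not for one arm's proportion, and the interval for the difference in that example stays within bounds.

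**Conclusion.** The concern holds in limited form. The stated model cannot be fitted to GPE because its required covariate does not exist, and a Gaussian constant-variance model is the wrong type for a dichotomy. Without the covariate, the estimate is a valid risk difference, but its standard error can be off in opposite directions at the two visits. The error ranges from nothing to about 18% too small at 8 weeks and 37% too large at 60 weeks, over the scenarios shown. These sizes rest on assumed response rates, equal rates in the two arms at each visit, and about 26 per arm; the protocol gives no expected GPE rate.

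Severity is moderate. One of seven secondary outcomes is affected. It would be wrong to infer that the conclusion on pain is at risk: the VAS outcome is continuous, has a baseline, and its analysis is untouched. Nor does GPE's place at the head of the list give it priority, since the protocol states no hierarchy among secondary outcomes.

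**What to change.** In the Statistical analysis section:

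1. Limit the baseline-adjusted linear mixed model to continuous outcomes that have a baseline measurement.
2. Name one model for dichotomised GPE. An example is a logistic GEE with group, time (8 and 60 weeks) and group × time, no GPE baseline term, and a small-sample variance correction because there are only about 26 participants per arm. Choose one model rather than offering alternatives: a GEE odds ratio is population-averaged and a mixed-logistic odds ratio is participant-specific, so they answer different questions.
3. State the effect measure: the risk difference with 95% CI at 8 and at 60 weeks, with the odds ratio as well if wanted.

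Baseline VAS as a covariate and an ordinal analysis of the seven categories are optional extras; the correction does not depend on them.

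The cost is one or two sentences. No data collection, visit or sample size changes, and the software the protocol already names can fit a logistic model for repeated data.
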